### **Recruitment**

#### *Pre-recruitment*

A pre-recruitment phase will occur at each participating health centre at which time mothers of children 9 to 11 months of age (who are not yet eligible to participate in the study) will be provided information on the study. They will be asked to return to the health centre on their child's first birthday at which time eligibility to participate in the study can be assessed. This step should facilitate recruitment, as well as help to ensure that children return to their health centre as close to their first birthday as possible.

#### *Recruitment*

During the recruitment phase of the study, eight project research nurses ('obstetriz') will each be present at one of the health centres during the morning CREDE clinics to recruit children into the study. The 'obstetriz' will obtain informed consent and administer the questionnaire to the parent/legal guardian, obtain the stool specimens for parasite assessment, obtain anthropometric measurements, assess cognitive and motor development, and administer the deworming (mebendazole) or placebo tablet.

Based on data provided by the eight identified health centres, approximately 200 to 250 children per month will be recruited for a total recruitment period of six months. Mothers routinely bring their children to the health centres in the mornings for check-ups and to receive their immunizations according to the Peruvian Ministry of Health schedule. A minimum response rate of 75-90% is expected based on previous experience working with this population.

### **Intervention groups**

Children will be randomized into one of the following four intervention groups, following their baseline assessment at the 12-month visit. Treatment will be with a single-dose mebendazole tablet (500mg) or identical (in smell, taste and appearance) placebo and provided during their routine CREDE visit:

**Group 1: Usual care and deworming at 12-month visit and usual care and placebo at 18-month visit.** Mebendazole will be given together with the standard health care package for 12-month-olds which includes administration of measles and rubella vaccine. Children in this group will not be dewormed at 18 months of age but will receive a placebo at this time along with the standard health care package for 18 month-olds which includes administration of the DPT (diphtheria, pertussis, and tetanus) vaccine booster.

**Group 2: Usual care and placebo at 12-month visit and usual care and deworming at 18-month visit.** A placebo will be given together with the standard health care package for 12 month-olds (i.e., measles and rubella vaccine). Children in this group will receive mebendazole at 18 months of age along with the standard health care package for 18 month-olds which includes administration of the DPT vaccine booster.

**Group 3: Usual care and deworming at both 12 and 18-month visits.** Mebendazole will be given together with the standard health care package for 12-month-olds which includes administration of measles and rubella vaccine. Children in this group will also receive mebendazole at the 18-month visit along with the standard health care package for 18 month-olds which includes administration of the DPT vaccine booster.

**Group 4: Usual care and placebo at both 12 and 18-month visits.** A placebo will be given together with the standard health care package for 12-month-olds which includes administration of measles and rubella vaccine. Children in this group will also receive a placebo at the 18-month visit along with the standard health care package for 18 month-olds which includes administration of the DPT vaccine booster.

All children will receive deworming at the end of the one-year follow-up (ie. the 24-month visit).

No problems regarding compliance are expected. The deworming tablet is single-dose and it will be crushed and mixed with a fruit purée for ease of administration. This crushed tablet will be administered in the presence of the ‘obstetriz’.

### **Randomization and treatment allocation**

Computer-generated randomly ordered blocks of eight and twelve will be used to randomly allocate children to each intervention group. This will ensure a balance in the number of children assigned to each group. Randomization will be stratified according to health centre. Sequentially numbered large envelopes will be prepared to meet the estimated sample size. Each large

envelope will contain the assigned intervention for each recruited child. Inside this envelope will be two smaller envelopes with the same ID number: one which will contain the intervention to be administered to the child at 12 months of age and one which will contain the intervention at 18 months of age. One pharmacist and one clinician-scientist not otherwise involved in the study will prepare envelopes containing the randomly chosen group intervention assignment in advance. Each 'obstetriz' will have a supply of 12-month envelopes containing the random intervention assignments at baseline. Once the single-dose mebendazole or placebo tablet is administered at the 12-month visit, the now empty 12-month intervention envelope will be stapled to each child's questionnaire (along with the signed informed consent form). This material will then be stored together at the research office with the corresponding 18-month envelope (with the same ID number) until the 18-month follow-up (at which time the tablet in the 18-month envelope will be administered to that child). Envelopes will be distributed among the recruitment sites until the sample size has been achieved.

### **Outcome measurements**

Prior to randomization, a baseline assessment will be conducted which will include anthropometry, and cognitive and motor development. A questionnaire will be administered to the child's mother to obtain socio-demographic information, medical history, feeding practices, and environmental exposure history. Stool specimens will be collected from all children (a small amount of fruit may be given to children, as needed, to facilitate a bowel movement. This method has been used successfully in the past and does not interfere with the quality of the stool). Follow-up assessments will be made at the 18-month CREDE visit, and at the 24-month CREDE visit, at which time all measurements will be repeated.

The primary outcome will be the mean weight gain between the 12 and the 24-month visit. Weight will be measured in duplicate using a portable electronic scale, accurate to the nearest 0.01 kg, calibrated daily using standard weights (Seca 334, Seca Corp., Baltimore, MD, USA).

Additional secondary measurements include length, cognitive and motor development and the prevalence and intensity of STH infections. Length (the recommended measurement of height in children < 30 months of age) will be measured in duplicate as recumbent crown-heel length on a flat surface using a measuring mat (Seca 210, Seca Corp., Baltimore, MD, USA), accurate to the nearest millimetre. Previous studies conducted by the proposed team in the Belén area showed inter and intra-rater reliability of over 95% for length/height and weight assessments (data not published), which are considered acceptable levels for anthropometric measurements. Cognitive and motor development will be assessed using the Bayley scale for cognitive and motor development (Bayley Scales of Infant and Toddler Development, Third Edition. Pearson Education Inc, Texas).

Stool specimens will be collected from all children to assess the prevalence and intensity of STH infections. All stool specimens will be transferred to the laboratory at the local research office (the Asociación Civil Selva Amazónica); however, at the 12-month visit, only specimens from children receiving deworming treatment will be examined for the presence and intensity of STH infection (e.g. *Ascaris*, *Trichuris* and hookworm). At the 18-month CREDE visit, only stool specimens from children receiving deworming treatment will be analyzed. One member of the research team will be unblinded to treatment status to arrange for the appropriate specimens to be

analyzed. (All other research personnel will remain blinded to maintain the double-blinding of the trial). This approach to examining stool specimens from identified treatment groups is required so that children found infected will be treated, thus meeting the ethical requirement to treat children who are known to be infected (based on a positive stool specimen). This approach also ensures that a baseline (at 12 months) and interim (at 18 months) estimate of worm prevalence, and worm intensity (which requires a fresh stool specimen) is obtained. These specimens which are to be analyzed immediately will be examined by a trained microscopist using the Kato-Katz method. This is the recommended technique for assessment of the prevalence and intensity (eggs per gram) of intestinal parasitic infection in fresh stool . For a one-stool specimen, sensitivity and specificity are over 96% for *Ascaris* and over 91% for *Trichuris* . There is lower sensitivity and specificity for hookworm; however, hookworm infection prevalence is negligible in this age group, so this should not bias the results.

Stool specimens from children receiving usual care and placebo at 12 and/or 18 months will be preserved in sodium acetate-acetic acid-formalin (SAF) and analyzed upon completion of the study using the ether-concentration method, the recommended technique for estimating worm prevalence from preserved samples.

At the 24-month visit stool specimens from all four groups will be immediately analyzed using the Kato-Katz technique (as all will be receiving deworming). At this time, efficacy of the deworming treatment will also be assessed in a random sample of 100 infected children. Stool specimens for the efficacy study will be obtained on three consecutive days, 10 days after treatment.

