### **Analyses**

#### *Primary analysis*

The results of the trial will be analyzed using an intention-to-treat approach. Following description of the study population at baseline, the mean weight gain between the first visit and the last follow-up (at the 24-month visit) will be compared between the four intervention groups using the one-way ANOVA procedure. While randomization should allow for approximately similar occurrence of determinants across the four intervention groups, adjustment for imbalances among the measured determinants and risk factors (e.g. history and duration of exclusive breastfeeding, timing of first introduction of complementary foods, home environment, family structure and characteristics and socioeconomic status) will be performed if needed using multivariate linear regression.

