#### *Secondary analyses*

Secondary analyses will be conducted to examine differences between groups in terms of derived weight indices (i.e. mean weight-for-age Z score and proportion of underweight), length (mean length gain, length-for-age Z score and proportion of stunting), cognitive and motor development (mean score) and STH prevalence and intensity. Means will be compared using a one-way ANOVA procedure and proportions will be compared using chi-square statistics. Adjustment for imbalances among measured determinants and risk factors will be conducted as needed, using multivariate linear or logistic regression for continuous and dichotomous outcomes, respectively. Length-for-age and weight-for-age Z scores will be calculated using the WHO Anthro software (Version 3, 2009), which compares growth in the study population to a WHO standard population. In addition to age, this method also takes into account the sex of the child. Cut-offs used to categorize the continuous variables of weight, length and eggs per gram are based on WHO standards for underweight (<-2 SD), stunting (<-2 SD) and STH intensity (low and moderate/heavy, according to parasite-specific egg counts), respectively.

To evaluate the possible modification of baseline anthropometry on the effect of deworming, multivariate regression models (e.g. linear for continuous variables and logistic for dichotomous outcomes) will be used with baseline weight and length included as interaction terms. This analysis is included to document the added value of deworming among young children who are already faltering. It will provide insight into both the preventive nature of deworming and also into whether deworming can reverse growth faltering that has already occurred by 12 months of age. Finally, possible intra-cluster correlation (by health centre), will be investigated using the intraclass correlation coefficient. If clustering is indeed detected, hierarchical logistic regression models will be used to obtain accurate estimates of treatment effects.

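### At 18 months the stool assay follows the tablet due at that visit, so four of the six pairwise STH comparisons carry an assay difference and a four-group intensity comparison cannot be made

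*Protocol*

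**What the plan says.** Protocol, Outcome measurements, decides which specimens are read fresh by the treatment given at the visit. For the first visit: "at the 12-month visit, only specimens from children receiving deworming treatment will be examined for the presence and intensity of STH infection". For the second: "At the 18-month CREDE visit, only stool specimens from children receiving deworming treatment will be analyzed". The method for these is stated: "These specimens which are to be analyzed immediately will be examined by a trained microscopist using the Kato-Katz method".

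The remaining specimens are handled differently: "Stool specimens from children receiving usual care and placebo at 12 and/or 18 months will be preserved in sodium acetate-acetic acid-formalin (SAF"). They are to be "analyzed upon completion of the study using the ether-concentration method, the recommended technique for estimating worm prevalence from preserved samples". The same section says that intensity is obtained only from the first kind of specimen: "worm intensity (which requires a fresh stool specimen"). At 24 months all four groups are read by Kato-Katz.

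Research Design has STH infection evaluated at 12, 18 and 24 months, and Objectives makes lower STH prevalence and intensity a secondary objective. Secondary analyses lists STH prevalence and intensity among the outcomes to be compared between groups. Means go to one-way ANOVA, and "proportions will be compared using chi-square statistics". No visit is named for STH, and assay is not mentioned.

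**The concern.** A comparison of infection between groups is interpretable only if infection is detected in the same way in each of them. At 18 months it is not. Two groups are read on fresh stool by one technique. The other two are read on preserved stool, by another technique, after the study has ended. Any difference in sensitivity or specificity between the techniques then appears as a difference between groups.

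At stake is a stated secondary outcome at the interim visit. A four-group test could reject with no drug effect, and single pairs could overstate, understate or reverse a real effect. For intensity the problem does not depend on accuracy: half of the groups would have no value to compare.

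**Working it through.** **Step 1. Map assay to group and visit** (from Intervention groups and Outcome measurements).

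| Visit | Group 1 | Group 2 | Group 3 | Group 4 |
|---|---|---|---|---|
| 12 months | Kato-Katz | ether | Kato-Katz | ether |
| 18 months | ether | Kato-Katz | Kato-Katz | ether |
| 24 months | Kato-Katz | Kato-Katz | Kato-Katz | Kato-Katz |

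**Step 2. Separate treatment from assay at 18 months.** Only the 12-month tablet can have acted by then: mebendazole in Groups 1 and 3, placebo in Groups 2 and 4. The assay follows the 18-month tablet. The six pairs are:

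- 3 vs 2 (both Kato-Katz) and 1 vs 4 (both ether): same assay, each a randomised contrast of 12-month mebendazole with placebo.
- 1 vs 2 and 3 vs 4: treatment effect mixed with assay.
- 1 vs 3 and 2 vs 4: same treatment so far, different assay, so any systematic difference is assay alone.

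**Step 3. Intensity.** It needs fresh stool. It is therefore absent for Groups 2 and 4 at 12 months and for Groups 1 and 4 at 18 months.

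**Step 4. Size of the prevalence artefact.** The protocol states no figure to reproduce. Inputs:

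- True 18-month prevalence p = 0.50 (Background, section on STH and malnutrition).
- Kato-Katz sensitivity 0.96 (*Ascaris*) or 0.91 (*Trichuris*); the protocol says over 96% and over 91% (Outcome measurements).
- Group size: 440 × 0.80 = 352, the full 20% attrition already lost at 18 months; or 440 × 0.90 = 396, half of it lost (assumption).
- Ether-concentration sensitivity s: not given; varied from 0.60 to 1.00 (assumption).
- Specificity 1 for both methods (assumption).

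Apparent prevalence = p × sensitivity. For Kato-Katz at 0.96 and s = 0.80 it is 0.50 × 0.96 = 0.48 against 0.50 × 0.80 = 0.40, a false gap of 8 points.

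For the four-group chi-square the noncentrality is λ = n Σ(pᵢ − p̄)² / [p̄(1 − p̄)]. With n = 352 in this example, p̄ = 0.44 and λ = 352 × 4 × 0.04² / (0.44 × 0.56) = 9.14. On 3 degrees of freedom (critical value 7.81) the rejection probability is 0.72. All results under no drug effect, nominal level 5%:

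| Ether sensitivity | Gap, Kato-Katz 0.96 | False rejection, n = 352 / 396 | Gap, Kato-Katz 0.91 | False rejection, n = 352 / 396 |
|---|---|---|---|---|
| 0.60 | 18.0 points | >99% / >99% | 15.5 points | >99% / >99% |
| 0.70 | 13.0 | 99% / >99% | 10.5 | 94% / 96% |
| 0.80 | 8.0 | 72% / 77% | 5.5 | 39% / 43% |
| 0.90 | 3.0 | 14% / 15% | 0.5 | 5% / 5% |
| 1.00 | −2.0 | 9% / 9% | −4.5 | 26% / 29% |

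**Step 5. Effect on pairs when the drug works.** Assume 50% truly infected without and 40% with 12-month mebendazole, Kato-Katz 0.96 and ether 0.70. Apparent prevalence: Group 1, 0.40 × 0.70 = 28.0%; Group 2, 0.50 × 0.96 = 48.0%; Group 3, 0.40 × 0.96 = 38.4%; Group 4, 0.50 × 0.70 = 35.0%. The true difference is −10 points.

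- 1 − 2 = −20.0 (overstated); 3 − 4 = +3.4 (wrong sign).
- 3 − 2 = −9.6; 1 − 4 = −7.0 (right sign, attenuated).
- Risk ratios of the same-assay pairs: 38.4/48.0 = 0.80 and 28.0/35.0 = 0.80. Odds ratios are about 0.68 and 0.72. Under these assumptions only the risk ratio is common to the two assays.

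**Step 6. Baseline.** At 12 months (prevalence 30%, Kato-Katz 0.96) the false gap is 0.30 × (0.96 − s): 7.8, 4.8 and 1.8 points at s = 0.70, 0.80 and 0.90.

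**The case against.** **The split is deliberate.** It follows from the protocol's stated duty to treat children known to be infected. That explains why placebo children's stool is not read at once. It does not make the two readings comparable, and the fix leaves specimen handling alone.

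**No 18-month four-group test is spelled out.** The protocol calls these readings a baseline and an interim estimate, which can be read as descriptive, and the choice of visit is often left to an SAP. This has weight. Against it, Research Design evaluates STH at all three visits and Secondary analyses sets a between-group method for STH without limiting it to one. A four-group intensity comparison at 18 months is ruled out by the protocol's own account of intensity, whatever an SAP says.

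**The size is assumed.** This stands. If ether-concentration is about as sensitive as Kato-Katz, the prevalence artefact vanishes. If it is more sensitive, the artefact changes sign.

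**Stronger readings that the protocol does not support:**

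- A reader might infer that treatment and assay are also mixed at 12 months. The baseline assessment precedes randomisation, so there is no treatment effect to mix. Only baseline comparability suffers.
- A reader might infer that nothing before 24 months is usable. Groups 3 vs 2 and 1 vs 4 are free of the assay difference at 18 months.
- A reader might infer that the false baseline imbalance will enter the weight model. Primary analysis foresees "adjustment for imbalances among the measured determinants and risk factors", if needed, but its open list of examples does not name STH. Adjustment for it is a possibility, not a stated plan.

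**Conclusion.** The point holds for STH prevalence and intensity at 18 months. As written, four of the six pairs differ in assay, and intensity is missing for two of the four groups. Both follow from the text without any assumption.

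The size and direction of the prevalence artefact cannot be fixed from the protocol. With 50% prevalence, specificity 1 and no drug effect, it runs from none to near-certain false rejection, depending on the gap between the two sensitivities. Large distortion needs ether-concentration to be clearly worse than Kato-Katz.

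At 12 months the harm is limited to a baseline STH value that is not comparable across groups and may show a false imbalance. The 24-month STH comparison and the primary outcome, weight gain, are unaffected. Severity: should be fixed. It concerns one secondary outcome at an interim visit and can be corrected before analysis.

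**What to change.** Amend Secondary analyses to state:

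- (a) The four-group comparison of STH prevalence and intensity is made at 24 months only.
- (b) At 18 months, prevalence is compared only within assay, Group 3 vs 2 and Group 1 vs 4. The two are combined as an assay-stratified Mantel-Haenszel risk ratio. The scale must be named, because risk differences and odds ratios would differ between assays even with one common effect. The common risk ratio itself presumes specificity near 1 and the same sensitivity in treated and untreated children within an assay.
- (c) At 18 months, intensity is compared for Group 3 vs 2 only.
- (d) STH at 12 months is reported by assay, and is neither tested nor adjusted for across assays.

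This needs analysis wording only: no new specimens and no change to treatment or laboratory procedures. The cost is that the 18-month four-group STH comparison is given up and 18-month intensity rests on two groups.

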### **Loss to follow-up**

A 20% rate of attrition has been estimated after 12 months of follow-up. This estimate is based on over eight years of experience in the area which has included follow-up with pregnant women (less than 10 % loss to follow-up over 7 months)  and new mothers (less than 18 % loss to follow-up after 8 months). High participation rates and follow-up will be encouraged by providing reimbursement to cover travel costs (the equivalent of a roundtrip bus ticket) for each of the two follow-up visits (an incentive previously acceptable to both Canadian and Peruvian ethics committees). Mothers have a booklet that they bring to each routine CREDE visit so that essential information can be recorded and the following visit can be scheduled. This should also facilitate the scheduling of the follow-up visits. A higher attrition rate of 20% has been accounted for in the proposed study due to the longer follow-up time of 12 months.

### **Standardization and quality control**

#### *Pre-recruitment training of field workers*

Prior to commencing recruitment, in-depth practical training of the research nurses ('obstetrices') will take place according to WHO guidelines . An experienced anthropometrist from the Instituto de Investigación Nutricional (IIN) in Lima will conduct the training to ensure correct techniques for obtaining length and weight measurements. The anthropometrist will be designated as the "gold standard" to which observations from 'obstetrices' will be compared and standardized. 'Obstetrices' will work in pairs and record length and weight for 10 – 15 children between 12 and 24 months of age (who will not be part of the proposed trial). If the difference between 'obstetrices' is greater than 100g for weight or 7mm for length, measurements will be

re-taken to a maximum of three times. Precision will be assessed using the inter- and intra-rater technical error of measurement (TEM) and will be considered adequate if they are within the expert's 95% precision margin. An experienced social scientist will train 'obstetrices' on the administration of the Bayley scale for cognitive and motor development.

